## Methods and statistical analysis

### Design

This study has a mixed factorial-experimental nested design. In total, each couple engages four times in the emotional sharing task, twice in the co-rumination and twice in the natural sharing condition. Each participant will twice share a distressing experience and will twice act as supporter. Both aspects will be experimentally manipulated between participants. Measures of mood and appraisal will be nested within participants, while movement and cardiovascular synchrony will be nested within dyads. The chronic variables (i.e., dyadic coping and relationship variables) will be used correlational.

### Participants

Couples aged 18–65 in a romantic relationship of at least 4 months will be eligible for participation. Participants also must be proficient in the Dutch language. Exclusion criteria are the use of psychoactive medications and a history of neurological conditions. The data collection for the ongoing study is actively underway, with participant recruitment expected to be completed by 31/12/2024. Recruitment for this study began on 01/01/2024 and will end on 31/12/2024.

### Sample size determination

We determined the sample size based on a priori power analysis (G*Power) [21]. For a power of at least 80% to compare the means of two independent groups, a minimum sample size of 128 dyads is required to detect medium effects (0.5) at α < .05 for two-tailed comparisons. A minimum sample size of 59–114 dyads is required to detect small effects (0.1–0.2) at α < .05 for linear multiple regression. We aim to recruit a sample size of 150 dyads for our study, so that we will be able to accommodate potential exclusions of participants due to unforeseen reasons. Compared to other studies on synchrony [22,23], our study features a large sample size.

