#### Chronic timescale.

***Relationship quality and dyadic coping analysis:*** We will employ regression analysis to examine the associations between relationship quality and dyadic coping strategies and movement and cardiovascular synchrony (*Hypothesis 7.1 and 7.2*). Additionally, to analyse whether dyadic coping and relationship quality are associated with mood changes we will add these variables as fixed factors in the linear mixed models built for testing hypothesis 3 on mood change over time (*Hypothesis 7.3*). Linear regression analyses will also be used to assess whether relationship quality and dyadic coping are related to emotional appraisal change (*Hypothesis 7.4*).

To assess whether co-rumination versus natural sharing influences the relationship between higher relationship quality and more constructive dyadic coping and movement and cardiovascular synchrony moderated regression analyses will be used (Hypotheses 8.1 and 8.2). To analyse whether the associations between relationship quality and dyadic coping with mood change are associated with effects of co-rumination versus natural sharing we will extend the linear mixed models used for testing hypothesis 7.3. The full model will consist of a random intercept for participants, fixed factors of assessment time and condition, their interaction, and mood as the dependent variable (*Hypothesis 8.3*). Moderated linear regression analyses will be used to assess whether better relationship quality and dyadic coping are associated with weaker effects of the co-rumination condition versus natural sharing on emotional appraisal change (*Hypothesis 8.4*).

The hypotheses presented in Table 1 and the data analysis techniques utilized constitute the core elements of our research. Additionally, we have identified and measured a range of secondary variables that could potentially influence these associations. Our aim is to incorporate these variables as covariates in the analyses to enhance our understanding of the findings. For all statistical tests α ≤ 0.05 (two-tailed) will be applied. Given the wide range of statistical tests performed, there is a concern regarding multiple comparisons. Therefore, to reduce the likelihood of Type I errors, we will apply the Bonferroni correction to all previously mentioned test results.

***Exploratory analyses summary:*** In our study, we plan to conduct exploratory analyses to investigate interpersonal synchrony in verbal communication:

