## Discussion

The planned research seeks to comprehensively evaluate interpersonal emotion regulation across phasic, tonic, and chronic time scales concurrently. This research design will allow for the examination of three leading theories of interpersonal emotion regulation—namely, synchrony [5], emotional sharing [8], and dyadic coping [12]. These theoretical frameworks and associated processes have so far not been studied within a single research design. By so doing, the planned research will allow us to examine how moment-to-moment (phasic) processes in interpersonal emotion regulation are related to specific episodes (tonic) of interpersonal emotion regulation, and how these, in turn, are related to more enduring (chronic) patterns in interpersonal emotion regulation.

The planned study -like all research- has limitations. First, the study’s generalizability may be limited due to its inclusion of only Dutch-speaking participants with a limited age range and relationship duration. Replicating the planned study with more diverse samples will be important to test the external validity of the findings. Second, the present study contains an experimental manipulation of one tonic process (i.e., co-rumination), but not of phasic processes (movement synchrony and cardiovascular synchrony) or chronic processes, which are both merely measured. Thus, the present study cannot draw causal conclusions about the role of phasic and chronic processes in interpersonal emotion regulation. Third, the study is limited by its reliance on retrospective self-reports for chronic processes and the potential participant fatigue from completing four emotional sharing conversations. While our within-subject design enhanced comparability across conditions, future studies could consider between-subjects or longitudinal designs to reduce participant burden and allow for more direct testing of chronic interpersonal processes over time.

Despite these caveats, the proposed study will be the first to study processes of interpersonal emotion regulation jointly across phasic, tonic, and chronic time scales. We hope that this study will facilitate the development of an integrated theoretical framework for understanding interpersonal emotion regulation.

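### The power statement assumes independent groups, an uncorrected α and an overall regression test, so it matches neither the within-couple design nor the Bonferroni rule; the shortfall lies in the regression claims, not the condition contrast

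*Protocol article*

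**What the plan says.** All places are in the protocol article.

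- **Sample size determination**, condition comparison: "to compare the means of two independent groups, a minimum sample size of 128 dyads is required to detect medium effects (0.5" on a standardised scale, with 80% power, "to detect medium effects (0.5) at α < .05 for two-tailed comparisons".
- **Sample size determination**, regression: "A minimum sample size of 59–114 dyads is required to detect small effects (0.1–0.2", again at α = .05. The metric of 0.1–0.2 and the number of predictors are not given. The recruitment target is 150 dyads, the margin being for exclusions.
- **Design**: "each couple engages four times in the emotional sharing task, twice in the co-rumination and twice in the natural sharing condition". The same paragraph then says of condition and role: "Both aspects will be experimentally manipulated between participants".
- **Co-rumination manipulation**: each partner is instructed once to co-ruminate and once to respond naturally.
- **Discussion**: "our within-subject design enhanced comparability across conditions".
- **Data analysis plan**: condition, mood and appraisal change are tested with multilevel or linear mixed models. Regression is planned for H7.1, H7.2 and H7.4, and moderated regression for H8.1, H8.2 and H8.4. At the end of the Chronic timescale subsection: "we will apply the Bonferroni correction to all previously mentioned test results".

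**The concern.** The sample size paragraph is the article's only justification for 150 couples, and it differs from the rest of the plan in three ways.

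1. It treats the conditions as two independent groups, although they are crossed within couple and within person.
2. It uses α = .05, although no confirmatory result will be judged at .05 once Bonferroni is applied.
3. Its regression figures appear to describe an overall model test, while H7 and H8 ask about one predictor or one interaction at a time.

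A reader will take it that 150 couples give 80% power to find small associations with relationship quality and dyadic coping, at the level used for decisions. A null result on H7 or H8 could then be read as informative when it is not.

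**Working it through.** **Inputs.** From the article: power 80%, effect 0.5, α = .05 two-sided, N = 128; regression effects 0.1–0.2, N = 59–114; target 150. Assumed: the size m of the Bonferroni family, because the article's text does not give it. I use m = 8 (one test per hypothesis) and m = 24 (H1–H2: 2 hypotheses × 2 synchrony outcomes = 4; H3–H6: 4; H7 and H8: 2 × 4 outcomes × 2 chronic predictors = 16). So α is .05/8 = .00625 or .05/24 = .0021.

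**Step 1: reproduce the stated figures.**
- Two-sample t-test, noncentrality d√(n/2) with n per group. For d = 0.5, α = .05: n = 63 gives power 0.795 and n = 64 gives 0.801. Total 128, as stated.
- Regression, noncentral F with noncentrality f²·N, overall test of three predictors: f² = 0.20 gives N = 59 and f² = 0.10 gives N = 114, both exact. With 1–8 predictors, overall or single-coefficient tests, and 0.1–0.2 read as f², r or R², no other variant tried matches. Read as r with one predictor, the range is 191–779; read as R² with three predictors, 48–103.
- In terms of R² = f²/(1 + f²): 0.10/1.10 = 0.09 and 0.20/1.20 = 0.17.

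The arithmetic in the paragraph is therefore correct. The question is what it is applied to.

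**Step 2: the condition contrast as a paired comparison.** Take one score per condition per couple, within-couple correlation ρ, dz = d/√(2(1 − ρ)), and a one-sample noncentral t. For d = 0.5:

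| ρ | dz | couples for 80%, α = .05 | couples for 80%, α = .05/24 | power with 128 couples, α = .05/24 |
|---|---|---|---|---|
| 0 | 0.354 | 65 | 128 | 0.80 |
| 0.3 | 0.423 | 46 | 91 | 0.95 |
| 0.5 | 0.500 | 34 | 67 | 0.99 |

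The stated 128 is still enough at the stricter α.

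**Step 3: the regression claim at the corrected α.** Overall test, three predictors:

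| f² | N | α = .05 | α = .05/8 | α = .05/24 |
|---|---|---|---|---|
| 0.10 | 114 (stated) | 0.80 | 0.53 | 0.39 |
| 0.10 | 150 | 0.91 | 0.71 | 0.58 |
| 0.20 | 59 (stated) | 0.80 | 0.51 | 0.37 |
| 0.20 | 150 | >0.99 | 0.98 | 0.96 |

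At f² = 0.10, 80% power needs 174 couples at m = 8 and 204 at m = 24.

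**Step 4: single coefficients.** With 150 couples, three predictors in the model and f² = 0.10, power is 0.97 at .05, 0.86 at .05/8 and 0.77 at .05/24. At f² = 0.02 it is 0.41, 0.15 and 0.08. The value 0.02 is the usual convention for a small effect and is an assumption here, since the article does not give it.

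**Step 5: smallest effects detectable with 80% power.**

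| Test | couples | α = .05 | α = .05/24 |
|---|---|---|---|
| Paired contrast, dz | 128 | 0.25 | 0.35 |
| Paired contrast, dz | 150 | 0.23 | 0.33 |
| Single coefficient, f² | 128 | 0.06 | 0.12 |
| Single coefficient, f² | 150 | 0.05 | 0.11 |

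**The case against.** The best defence is that nothing is miscalculated, that the independent-groups assumption is conservative, and that linear regression is a planned method. All of this stands. Several stronger readings a reader might draw are not supported.

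- **That the condition contrast is underpowered.** Applying .05/24 to the two-group t-test gives 38% power with 128 and a requirement of 252. But that test will not be run. For the within-couple contrast, step 2 shows that the planned number is adequate at d = 0.5.
- **That the stated 80% relates to no planned analysis at all.** H7.1, H7.2, H7.4 and the corresponding parts of H8 use regression. A moderator, condition and their interaction would make three predictors, though H8 rests on the interaction alone. The comparison of real with pseudo-dyads in H1 is the nearest thing to a two-group test, although those groups share people.
- **That the small regression effects exceed the medium mean difference.** Converting d = 0.5 gives f² = d²/4 = 0.0625, but that is a one-degree-of-freedom effect. Spread evenly over three uncorrelated predictors, 0.10 is about 0.033 each. The two numbers are not comparable.
- **That H8 and H7.3 cannot detect small effects.** H8 crosses a within-couple factor with a couple- or person-level moderator, and H7.3 is a mixed model. Power for both depends on a within-couple correlation that the article does not give.

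The number of tests is also an assumption. The detailed hypotheses are in Supplementary 1, which is not shown.

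**Conclusion.** The power statement is wrong as written: it matches neither the design nor the rule by which results will be judged. The consequences differ by hypothesis.

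- **Condition contrasts:** the statement is conservative about the design. With ρ ≥ 0 and one score per condition per couple, 128 couples give about 80% power or more for d = 0.5 at .05/24.
- **Regressions:** the claim fails at the corrected α. At f² = 0.10, the stated 114 gives 39–53% power and the recruited 150 gives 58–71%, over 24 to 8 assumed tests. At f² = 0.20, 150 couples remain sufficient, so the gap concerns the lower end of the stated range.
- **The word small:** if it is read in the usual sense (f² = 0.02), one coefficient has 41% power with 150 couples even before correction.

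The paired and single-coefficient figures only approximate the planned multilevel models. The upper values suppose that all 150 couples are analysed.

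**What to change.** Keep 150 couples and rewrite the paragraph:

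1. State the number of tests in the Bonferroni family and the resulting α.
2. Replace the two power sentences with detectable effects at that α for the tests to be run, labelled as approximations, for 128–150 analysable couples. With 24 tests these are the step 5 values: paired dz about 0.35–0.33 and single-coefficient f² about 0.12–0.11. The uncorrected values can stand beside them.
3. For the H8 within-couple interactions and the mixed models, give values over a stated range of within-couple correlation.
4. Name the effect-size metric and number of predictors, and delete the description of the regression effects as small.
5. Correct the Design sentence so that it agrees with the within-couple allocation described in the rest of the article.

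The cost is wording, plus a short power calculation for item 3. The stated sensitivity for H7 and H8 becomes less favourable. Replacing Bonferroni with Holm would keep the same family-wise control and never lose power, but it is optional: Bonferroni is valid.

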### Procedure

Participants will be recruited partly through a recruitment agency and partly by research assistants spreading flyers on the university campus, making announcements to the participant pool of the psychology program at the Vrije Universiteit Amsterdam and by recruiting from their social networks. Interested individuals will be asked to complete a brief online questionnaire to assess their eligibility. To reduce random error in psychophysiological responses an email will be sent to the participants two days before the experimental session, with the request to refrain from alcohol consumption and intense physical activity 24 hours before the session, and caffeine consumption 2 hours before the session.

Participants will arrive as a couple and will be personally greeted by a research assistant at the building entrance and escorted to the laboratory. A diagram of the laboratory is shown in Fig 1 and a photograph of the lab space is shown in Fig 2. Upon arrival at the lab, the couple will be greeted by a second research assistant. Each participant will be led to their individual workspace. Next, the experimental procedures will be explained to the participants by the research assistants and written informed consent will be obtained. After these explanations, participants will verify their compliance with the behavioural instructions. Divergences of the behavioural instructions will be noted and included as covariates to control for their effects. To do so, we will record participants’ alcohol consumption (yes or no), their physical activity intensity (5-point score, from ‘none’ to ‘very strong’) and caffeine digestion (1 mug to 5 mugs).

**Fig 1 pone.0323526.g001:**
[figure not shown]
Diagram of the interaction laboratory and observation room.

**Fig 2 pone.0323526.g002:**
[figure not shown]
Photograph of the emotional sharing space and one individual workspace.

In the first phase of the experiment, participants will be asked to rate their mood on the mood adjective checklist (BEF) [24]. Then they will be instructed to generate two personal negative experiences using the Experience-Generation Questionnaire (EGQ) [25]. Subsequently, the Experience Scales (ES) [26] will be used to tap into their appraisal of these two experiences. Next, participants will be fitted with the sensors of the Vrije Universiteit - Ambulatory Monitoring System (VU-AMS). Once the VU-AMS has been set up, participants will be requested to complete the pre-sharing survey.

Subsequently, participants will be provided with instructions for the emotional sharing task, consisting of four dialogues. Upon completion of the entire emotional sharing task, participants will complete a post-sharing survey and the ECG device will be removed. Finally, participants will be debriefed, rewarded, and thanked. Fig 3 shows the whole experimental session. In total, the experiment takes approximately 2 hours, with task instructions taking 10 minutes, device fitting taking 15 minutes, the pre-sharing survey taking 15 minutes, the emotional sharing task for four episodes lasting 60 minutes, the post-sharing survey taking 15 minutes, and the device removal and closure taking 5 minutes.

**Fig 3 pone.0323526.g003:**
[figure not shown]
Experimental session.

### Experiences generation task

In the emotional sharing tasks, participants will be asked to talk about two negative experiences from their own life. To illustrate what is meant by negative experiences, the ERQ lists seven negative experiences, such as having an argument with a close friend or family member. Participants will be asked to write down two negative experiences they are currently facing. By focusing on personal experiences, we ensure that the study has high personal relevance for the participants.

### Emotional sharing task

The emotional sharing task, which is modelled after Nils & Rimé (2009), involves a structured procedure to make participants share their emotions in a controlled experimental setting [13]. Participants will be having a total of four eight-minutes episodes with their partner to share the two experiences they each wrote down in the experience generation task. During each episode, one participant will act as a sharer (to discuss the problem) and the other participant will act as a supporter (to listen and respond to the sharer). The roles of sharer and supporter will be randomly alternated so that each participant will be a sharer and a supporter twice.

### Co-rumination manipulation

We will experimentally manipulate the instructions of the emotional sharing task, following a validated procedure developed by Tudder et al (2023) [27]. For half of the sharing episodes, the supporter will receive instructions that promote co-rumination, which involves focusing on a topic, repeatedly discussing the issues, speculating about the antecedents and consequences of the issues, and exploring and unearthing negative emotions. For the other sharing episodes, the supporter will be instructed to respond in a natural way to the sharer. The order of the co-rumination versus natural response will be counterbalanced. Each member of the couple will be instructed once to engage in co-rumination and once to engage naturally with the sharer in all four conditions, the participants will receive digital instructions and physical cards to remind them of their role and the associated instructions.

Before the first sharing episode, participants will be taken by their experimenter to the emotional sharing space with the two armchairs (see Fig 1b), so that they can familiarize themselves with this space Then they will be taken back to their private space, where they will be informed about the first experience to address and be asked to “collect their thoughts” for two minutes. Following this, each participant will again be taken to the emotional sharing space. Participants will then engage in their first round of emotional sharing on the selected experience. After completing the first emotional sharing episode, the participants will go back to the private space and complete the post-dialogue survey about their sharing experience. After completing the first instruction, the instructions for natural sharing and co-rumination will be reversed, and after two rounds, the roles of the sharer and supporter will be switched, and vice versa.

### Ethical considerations

The protocol obtained approval from the Scientific and Ethical Review Board, Vrije Universiteit Amsterdam (protocol number VCWE-2023-130R1). All participants will provide written informed consent. During the data collection process, all study-related documents (data and informed consent forms) will be securely stored in Yoda (Your Data is a cloud storage at SURF and suitable for storing large-scale and sensitive datasets). After completion of the study, final storage and archiving of the electronic data will take place in a dedicated archive at Vrije Universiteit Amsterdam and will be processed in compliance with the General Data Protection Regulation (GDPR). In accordance with legal regulations from the European Union, the data will be stored for a period of 10 years.

### Measurement

Table 2 provides a comprehensive overview of the tools and objectives for the measurement employed in this study. More detailed information can be found in Supplementary 2 in S1 File.

**Table 2 pone.0323526.t002:** Overview of the measurement tools, objectives and measurement period.

Timescale	Name	Measurement objectives	Measurement period
*Phasic*	VRMS	Movement synchrony	Emotional sharing episodes
	CMS	Cardiovascular synchrony	Emotional sharing episodes
*Tonic*	BEF	Mood (e.g., *“Helplessness.”)*	Pre-sharing survey and post-dialogue surveys
	ES	Emotional Appraisal (e.g., *“How intense were the negative emotions that you had during this experience?”*)	Pre-sharing survey and post-dialogue surveys
	IOSS	How close the respondent feels with another person (seven images)	Pre-sharing survey and post-dialogue surveys
	SOE	The experiences of partners in conversation (e.g., *“I felt completely like myself during the conversation.”*)	Post-dialogue surveys
	PPR	Individuals’ perceptions of their partners’ responsiveness (e.g., *“My partner understood me.”*)	Post-dialogue surveys
	IER-DSFP	Different interpersonal emotion regulation strategies from partner (e.g., *“My partner tried to get me to talk over and over about what is bothering me.”*)	Post-dialogue surveys
	RQ-ASSC	Relationship quality (e.g., *“My partner and I agreed on how I could best approach the problem.”*)	Post-dialogue surveys
*Chronic*	DCI	Dyadic coping strategies (e.g., *“I tell my partner that it is not that bad and help him/her to see the situation in a different light.”*)	Pre-sharing survey
	PQ-SF	Quality of romantic relationships (e.g., *“He/she takes me in his arms.”*)	Pre-sharing survey
	PSAS-SF	Attachment styles (e.g., *“It helps to turn to my partner in times of need.”*)	Pre-sharing survey
	TAS-20	Alexithymia (e.g., *“I am often confused about what emotion I am feeling.”*)	Pre-sharing survey
	OSRS	Participants’ perception of emotion regulation (e.g., *“I gave someone helpful advice to try to make them feel better.”*)	Pre-sharing survey
	SSL	Perceived social support received (e.g., *“Did you ask for help or advice?”*)	Pre-sharing survey
	SV	Sociodemographic variables (e.g., *“How old are you*.*”*)	Post-sharing survey
	UCLA-LS	Loneliness (e.g., *“I lack companionship.”*)	Post-sharing survey
	IRI	Empathy (e.g., “*I sometimes find it difficult to see things from the other person’s perspective*.”)	Post-sharing survey
	DDI	Distress disclosure (e.g., “*When I feel upset, I usually confide in my friends*”)	Post-sharing survey
	BSRI	Sex role (e.g., “ *Assess the extent to which the following characteristics apply to you: loving*”)	Post-sharing survey
	MHC	Total mental health (one item “ *How happy are you?*”))	Post-sharing survey

VRMS*:* Video recordings and movement synchrony, CMS: Cardiovascular measurement and synchrony, BEF: Mood adjective checklist, ES: Experience scales, IOSS: Inclusion of other in the self scale, SOE: Shearer/supporter’ own experience, PPR: Perceived partner responsiveness, IER-DSFP: Interpersonal emotion regulation with different strategies from partner, RQ-ASSC: Relationship quality: agreement, support, self-disclosure, closeness, TAS-20: The Toronto alexithymia-20 scale, PQ-SF: Partnership questionnaire—short form, PSAS-SF: Partner-specific attachment security short form, DCI: Dyadic coping inventory, OSRS: The others and self-emotion regulation scale, SSL: Social support list, UCLA: University Of California, Los Angeles, UCIA-LS: UCLA Loneliness Scale, IRI: Interpersonal reactivity index, DDI: Distress disclosure index, BSRI: Bem sex role inventory, MHC: Mental health continuum

